### Exclusion criteria

Exclusion criteria include other causes of liver disease such as viral hepatitis and alcoholic liver disease; cirrhosis of the liver (FibroScan >17.5kPa or FibroTest >0.8) or clinical features of cirrhosis; alcohol consumption >20 g/day (2 standard drinks) in women or > 30 g/d (3 drinks) in men; alternate (e.g. TPN) or concomitant etiology for abnormal liver enzymes; history of decompensated liver disease including ascites, encephalopathy or variceal bleeding; concomitant use of any weight loss medication or herbal weight loss products, previous bariatric or other intestinal surgery known to affect food intake or digestive function; presence of active infection, pregnancy or lactation; regular use of a probiotic or prebiotic supplement within 3 months prior to enrollment; antibiotic use within 3 months prior to enrollment; weight loss >3 kg within the preceding 3 months to enrollment; uncontrolled cardiovascular or respiratory disease, active malignancy, or chronic infections; use of agents such as vitamin E, omega-3 fatty acids or medications with evidence for effects on NAFLD (pioglitazone, GLP-1 analogues, dipeptidyl peptidase IV inhibitors, ursodeoxycholic acid); and patients with type 2 diabetes where HbA1c is >9 %.

### Randomization

Participants will be randomized in equal numbers to two groups, stratified by sex, BMI, and age for allocation into prebiotic or placebo arms. Randomization sequences will be prepared by an independent statistician and entered into a web-based central randomization program. Sequences will not be revealed to investigators or study staff. Randomization will be in blocks of 4 within each sex/age/BMI stratum. To maintain blinding of the trial coordinator and registered dietitian, a research assistant with no involvement in the study will use the central randomization program at the randomization visit. Study personnel will be unaware of treatment allocation prior to the assignment of interventions, using sequentially numbered, opaque, sealed envelopes to maintain allocation concealment. The clinical trial coordinator will enroll participants. Participants, research staff and outcome assessors will be blinded to participants’ assigned group. Participants will receive the prebiotic or placebo supplement in identical foil packets to maintain blinding. An overview of the study design and measurement outcomes is presented in Fig. 1.

**Fig. 1 Fig1:**
[figure not shown]
Schematic overviews of the **a** study design and **b** testing day protocols. *Blood work at Calgary Laboratory Services (CLS) includes: glucose, lipids (total, LDL, HDL, TG), HbA1C, liver enzymes (ALT, AST, ALP), FibroTest (gamma-glutamyl transpeptidase, bilirubin, α2-macroglobulin, haptoglobin, and apo-lipoprotein A1), CRP, and liver function biochemistries (creatinine, electrolytes, albumin, bilirubin). **Adipokines/Cytokines include: adiponectin, MCP-1, TNF-α, IL-6 and IL-8. ***Satiety hormones include: active ghrelin, insulin, leptin, total GIP, active GLP-1, and total PYY

Participants will be randomly assigned to a 16 g/day prebiotic dose [Synergy1 (oligofructose-enriched inulin), Beneo-Orafti, Belgium] or an equicaloric dose of placebo [maltodextrin] for 24 weeks. The dose will be ramped up over two weeks and at full dose be consumed as two 8 g packets/day (13.2 kcal/packet) or two 3.3 g packets/day (13.2 kcal/packet) of maltodextrin. Participants will add the packet to 250 ml of water and consume it 30 minutes prior to lunch and dinner. The dose of 16 g/d was selected given previous work showing a reduction in serum AST in NASH patients with prebiotic [85]. Compliance will be assessed via packet counts.

### Dietary weight loss intervention

All participants will be provided diet and lifestyle counseling in one-on-one sessions with a registered dietitian. Participants will be responsible for buying and preparing their own food. The diet will be designed to achieve a weight loss of 0.5-1.0 kg/week with an appropriate energy deficit based on anthropometrics and indirect calorimetry analysis. Participants will meet with the dietitian for 10 in-person visits (1–2 h each). Nutrition education and behavior modification strategies will be used to reduce intake of total energy, added sugars, sodium, and processed food, and to maintain adequate protein intake. Dietary intake during the phases will be assessed by weighed 3-day food records. The dietitian will also contact participants by phone each week to assess adherence, address questions or issues that arise, and monitor body weight. Body weight and waist and hip circumferences will be measured at each visit, and there will be a fasting blood draw at the midpoint of the study (week 12) to monitor blood chemistries (serum aminotransferases and lipids).

During the first phase (visits 1–4), participants will be provided with two 7-day meal plans designed by the dietitian. Meal plans will be personalized for each participants, taking into consideration lifestyle and food preferences based on questionnaires completed at screening. Nutrition education components will include identifying primary food sources of fat, carbohydrate, and protein, reading nutrition labels, and sources of empty calories. In the second phase (visits 5–8), the focus will be on behavior modification and achieving dietary autonomy. This will be achieved through specific counseling which will include planning and preparing meals in the home, portion control, and choosing foods when dining out. Counseling will also be tailored to each individual, based on initial questionnaires related to food craving and behavior. During the final phase (visits 9 and 10), participants will be entirely responsible for planning their own meals and counseling will focus on maintenance of dietary behaviors.

### Primary outcome

#### Hepatic injury and liver fat

The primary outcome is change in hepatic injury and liver fat from baseline to 24 weeks. Improvement in liver injury will be defined by reduction in non-invasive and biochemical markers of fibrosis and inflammation. Fibrosis will be measured at baseline and 24 weeks using transient elastography (FibroScan), which has a high sensitivity for diagnosis and prognostic stratification of varying degrees of liver fibrosis [86, 87] and the Fibrotest which is a composite of serological markers and age and sex, that provides a quantitative estimate of liver damage (age, sex, gamma-glutamyl transpeptidase, bilirubin, α2-macroglobulin, haptoglobin, and apo-lipoprotein A1) [88]. The newer XL probe, specifically designed for obese patients, will be used for FibroScan [86]. Magnetic resonance imaging (MRI) will be performed at baseline and 24 weeks on a 1.5 T scanner (GE Medical Systems, Milwaukee, USA) to assess change in liver fat. MRI can detect fat in microscopic quantities and with chemical shift imaging (CSI) has a sensitivity of 90 % and specificity of 91 % [89]. Although costly, MRI is a front-runner in imaging modalities to quantify hepatic steatosis and represents an acceptable alternative to invasive liver biopsy. While still the gold standard in histological assessment of NAFLD, biopsy is not without risk and is limited by its lack of representation of the liver as a whole [90].

### Secondary outcomes

#### Anthropometrics and Dual Energy X-Ray Absorptiometry

Height will be measured at the beginning of the study to confirm BMI. At each dietitian visit, body weight will be measured using a calibrated balance beam scale along with waist circumference and blood pressure. Body composition will be assessed at baseline and week 24 by DXA (Hologic QDR 4500, Hologic, Inc., Bedford, MA).

### Food record

Food and beverage intake will be assessed using 3-day weighed food records at baseline, 4, 10, 16 and 24 weeks using food scales and standardized forms provided to the participants. Dietary adherence will be defined as prescribed versus measured energy intake. Prior to the start of the study all participants will attend a training session delivered by the dietitian in which they will be instructed on the use of the food scale and how to record their food intake. Participants will then be instructed to weigh and record all food consumed for 2 weekdays and 1 weekend day. This information will be analyzed with FoodWorks software (The Nutrition Company, Long Valley, NJ). Food records will also be used to assess dietary adherence.

### Physical activity and sleep monitoring

Participants will be instructed to maintain their current level of physical activity throughout the study. Physical activity will be monitored at 0, 12, and 24 weeks using a modified Godin’s Leisure Time Exercise Questionnaire that includes duration [91]. Objective monitoring of sleep and physical activity will occur at baseline and 24 weeks. Participants will be provided with an ActiGraph wGT3X-BT (ActiGraph, Pensacola, FL) monitor initialised at 30Hz to wear for five consecutive days. Participants will be instructed to wear the monitor on their waist during waking hours (except when in contact with water) and on their wrist while sleeping, as the monitor has been validated in these positions [92]. At least 3 days of valid wear will be required for the data to be included in the analysis [93]. ActiLife6 software (ActiGraph, Pensacola, FL) will be used to convert data to 1-minute epochs. For physical activity, counts per minute will be classified using predetermined tri-axial vector magnitude cut-points for light, moderate, hard or very hard 0–2690, 2691–6166, 6167–9642, and >9642 counts per min respectively [94]. Sleep will be scored using the Cole Kripke algorithm [95] included in the ActiLife software.

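### The lowest accelerometer class starts at zero counts and is called light activity, so sitting still is scored as activity and the class largely tracks wear time

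*Protocol article*

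**What the plan says.** All the relevant text is in the protocol article, under physical activity and sleep monitoring.

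- The aim: "Participants will be instructed to maintain their current level of physical activity throughout the study". Compliance is followed by a leisure-time exercise questionnaire at 0, 12 and 24 weeks, and objectively by a body-worn monitor for five days at baseline and at 24 weeks.
- Position of the monitor: "on their waist during waking hours (except when in contact with water) and on their wrist while sleeping".
- Resolution: the software "will be used to convert data to 1-minute epochs".
- Inclusion of data: "At least 3 days of valid wear will be required for the data to be included in the analysis".
- Activity scoring: "For physical activity, counts per minute will be classified using predetermined tri-axial vector magnitude cut-points", with the limits "cut-points for light, moderate, hard or very hard 0–2690, 2691–6166, 6167–9642, and >9642 counts per min respectively".
- Sleep has a separate method: "Sleep will be scored using the Cole Kripke algorithm".

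The section on statistical analyses does not list physical activity as a primary outcome. Nor is it among the factors named for the ANCOVA, which are sex, BMI, age and fasting insulin.

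**The concern.** The article states a rule here, so this is not a detail left to a fuller document: the light class has a printed lower limit of 0. Sitting still and moving gently then fall in the same class, and the label describes both as activity.

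In a weight-loss programme, a shift between sitting and light movement is one of the changes an objective monitor should be able to show. Under the stated limits it cannot. A change in how long the monitor is worn while seated, however, will appear as a change in light activity. Someone comparing light minutes between baseline and week 24 could take more wear for more activity, or find no change when habits had in fact changed.

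**Working it through.** The article gives no activity totals, so there is no planned figure to reproduce. The first two steps follow from the stated limits alone. The others use assumed values, shown as ranges.

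**1. Do the classes cover everything?** The limits are 0–2690, 2691–6166, 6167–9642 and above 9642. Each class starts one count above the end of the one before (2690 + 1 = 2691; 6166 + 1 = 6167; 9642 + 1 = 9643), and the first starts at 0. Every scored minute falls in exactly one class, and none is sedentary.

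**2. What follows directly.** Write W for scored waking wear minutes, M for moderate, hard and very hard minutes together, and L for minutes classed as light. Then L = W − M.

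- Replace 60 sitting minutes by 60 minutes of light movement: W and M are unchanged, so L changes by 0.
- Wear the monitor 60 minutes longer while sitting: W rises by 60 and M by 0, so L rises by 60.

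**3. How much of wear time is called light?** Share = (W − M)/W, assuming W = 600 to 960 and M = 10 to 60 minutes per day.

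- Lowest: (600 − 60)/600 = 540/600 = 90%.
- Middle: (780 − 30)/780 = 750/780 = 96%.
- Highest: (960 − 10)/960 = 950/960 = 99%.

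**4. How much of the class is really light activity?** Let s be the fraction of wear spent sitting still, assumed to be 50 to 70%. True light share of the class = (W − M − sW)/(W − M).

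- Lowest: W = 600, M = 60, s = 0.7: (540 − 420)/540 = 120/540 = 22%.
- Middle: W = 780, M = 30, s = 0.6: (750 − 468)/750 = 282/750 = 38%.
- Highest: W = 960, M = 10, s = 0.5: (950 − 480)/950 = 470/950 = 49%.

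**5. How far does L track wear time?** If W and M are uncorrelated (assumption), the share of the variance of L that comes from W is SD_W²/(SD_W² + SD_M²). Take SD_M = 10 to 30 minutes.

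- SD_W = 60, SD_M = 30: 3600/(3600 + 900) = 80%.
- SD_W = 120, SD_M = 10: 14400/(14400 + 100) = 99%.
- SD_W = 30, SD_M = 30: 900/(900 + 900) = 50%.
- SD_W = 30, SD_M = 10: 900/(900 + 100) = 90%.

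So wear time accounts for 80 to 99% of the variance when its SD is 60 to 120 minutes, and for 50 to 90% when it is 30 minutes.

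**The case against.** The strongest reply is that this is a labelling matter in a monitoring variable. The moderate, hard and very hard minutes do not depend on where the light class begins, so a change in exercise at 2691 counts or above would still be seen. The questionnaire gives a second view of activity. No stated efficacy analysis uses the light class. The limits come from a cited source that cannot be checked here and that may intend the lowest class to include sedentary time. The percentages above rest on assumed days. All of this stands, and it keeps the point small. It does not remove it: the printed label is light, the printed lower limit is 0, and the questionnaire is self-report.

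A reader might also infer three stronger things that the article does not support.

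- *That night-time wrist wear is counted as light activity.* The cut-points are introduced as applying to physical activity, and sleep is given its own algorithm. The natural reading is two data streams with two scoring methods. Nothing in the text sends wrist-worn sleep minutes through the activity classes.
- *That a monitor taken off and lying still is counted as light activity.* The plan requires valid wear. How non-wear is detected is a processing step that a condensed article may leave to the full protocol.
- *That the rule could create or hide a difference in liver fat between the arms.* Activity enters neither the primary outcome nor the named covariates. Participants are randomised and blinded, and the article gives no reason why wear time should differ by arm.

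**Conclusion.** The point holds as a minor flaw in a stated rule. The class called light contains all motionless waking wear, cannot register a shift between sitting and light movement, and rises with longer seated wear. Those three statements need no assumption beyond the printed limits.

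The size is conditional. Light takes about 90 to 99% of wear time for 600 to 960 wear minutes and 10 to 60 moderate-or-harder minutes per day. Only about 22 to 49% of the class is true light activity if half to 70% of wear is sedentary. That the class mainly reflects wear time holds over most of the assumed SDs, but less clearly when wear time varies little between participants.

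The consequence is confined to the only objective check on maintained activity, and within it to the lowest class. The upper three classes and the primary comparison are not affected.

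**What to change.** - Split 0–2690 into a sedentary and a light class, using a vector-magnitude sedentary cut-point chosen and cited before the data are examined. If no split is wanted, at minimum rename the class sedentary and light.
- Report minutes in each class as a share of valid waking waist-wear time, so that a difference in wear is not read as a difference in activity.

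The two changes do different work. Without the split, the lowest class as a share is simply 1 − M/W, which adds nothing to the other three classes. Only the split lets the monitor distinguish sitting from light movement.

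The cost is one or two sentences in the protocol or analysis plan and a software setting. The 1-minute epochs already planned are sufficient, so no new data are needed. The small downside is one more class to report.

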### Subjective and objective assessments of appetite

Subjective ratings of appetite will be recorded by participants at home following a meal, at the same time on the same day, each week using a validated 100 mm VAS [96, 97]. The questions asked based on how the participant felt over the past week are:“How hungry do you feel?” anchored by “I am not hungry at all” and “I have never been more hungry”.“How satisfied do you feel?” anchored by “I am completely empty” and “I cannot eat another bite”.“How strong is your desire to eat” anchored by “I have no desire to eat” and “I have a great desire to eat”.“How full do you feel?” anchored by “Not at all full” and “Totally full”.“How much do you think you could eat?” anchored by “Nothing at all” and “A lot”.Over the course of the past week, my appetite was: “Much lower than usual” and “Much higher than usual”.

### Quality of life and gastrointestinal feelings

Quality of life will be measured at baseline and 24 weeks with the SF-36v2 Health Survey questionnaire [98]. This is a 36 question self-administered questionnaire used to measure functional health and well-being. Bowel habits and gastrointestinal feelings will be assessed at baseline, 12 and 24 weeks using our standard gastrointestinal feelings ratings form (abdominal comfort, bloating, flatulence, rumbling of stomach) and bowel habits questionnaire (number of bowel movements and Bristol Stool Chart).

### Oral glucose tolerance test (OGTT)

Participants will consume a standardized menu the day prior to the OGTT to ensure consistency in macronutrient consumption prior to testing. The menu has been designed by a dietitian and includes 3 meals and 2 snacks. Participants will be instructed to finish dinner and then to not eat after 8 pm. The following morning, a baseline blood sample will be taken via a cannula inserted into the antecubital vein. Subsequently, participants will consume a 75 g oral glucose drink and blood samples will be drawn at 30, 60, 120 and 180 minutes. The OGTT will be conducted at baseline and follow-up (24 weeks). Blood will be centrifuged and plasma frozen at −80 °C for future analyses. Glucose will be quantified using a glucose trinder assay (Stan Bio, Boerne, TX, USA) as per our previous work [72].

### Plasma lipids, liver biochemistry, and inflammatory markers

At baseline, 12 and 24 weeks, a fasting blood sample will be taken for measurement of plasma HbA1c, lipids, CRP, liver enzymes (ALT, ALP, AST), FibroTest, and biochemical markers of liver function (creatinine, electrolytes, albumin, bilirubin). Blood will be drawn at and analysed by Calgary Laboratory Services (Calgary, AB, Canada). Serum adipokines and inflammatory markers (adiponectin, MCP-1, TNF-α, IL-6 and IL-8) will be quantified using Milliplex kits (Millipore, Billerica, MA) from fasting samples obtained at baseline and follow-up (24 weeks) testing.

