### Statistical analyses

Statistical analyses will be performed using SPSS 22.0 software (IBM, Armonk, NY). Values with skewed distribution will be logarithmically transformed prior to analysis. Baseline characteristics will be compared between groups using chi-square for categorical variables and t-tests for continuous variables. Primary analysis will be performed on an intent-to-treat basis, regardless of subject compliance. The primary outcome measures are change from baseline to 24 weeks in hepatic injury (Fibrotest, FibroScan) and liver fat (percent measured by MRI). ANCOVA, with testing for confounding factors (sex) and potential covariates (BMI, age and fasting insulin) will be used to assess the difference between groups at weeks 0 and 24. Should the main effect of diet be significant, Tukey’s multiple comparison test will be used. Secondary outcomes measured at 0 to 24 weeks (e.g. satiety hormones, body fat, glycemia and insulinemia) will be analyzed with ANCOVA as above. For variables measured over time (e.g. body weight, satiety hormones and glucose at 0, 30, 60, 120 and 180 minutes), a mixed model of repeated measures ANCOVA will be applied to examine the effect of treatment, time and their interaction. Our planned secondary analysis will be per protocol with all participants who complete the 24 week intervention and are compliant based on consumption of ≥80 % the product doses. Cases with missing outcome data will be excluded from analysis. Results will be considered statistically significant (2-sided) at *P* ≤ 0.025 (Bonferroni adjustment for 2 primary outcomes).

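### Sections disagree on whether FibroTest, a primary measure, is drawn at week 12, and the stated analysis would leave a week-12 value unused

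*Protocol article*

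**What the plan says.** Three sections of the protocol article bear on the FibroTest schedule.

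- **Plasma lipids, liver biochemistry, and inflammatory markers:** the sampling sentence reads "At baseline, 12 and 24 weeks, a fasting blood sample will be taken for measurement of plasma HbA1c, lipids, CRP, liver enzymes"; its list then goes on to name FibroTest and further liver biochemistry. This gives weeks 0, 12 and 24.
- **Hepatic injury and liver fat (primary outcome):** "Fibrosis will be measured at baseline and 24 weeks using transient elastography (FibroScan"; the same sentence continues "and the Fibrotest which is a composite of serological markers and age and sex". This gives baseline and week 24 for both fibrosis measures. For liver fat, "Magnetic resonance imaging (MRI) will be performed at baseline and 24 weeks on a 1.5 T scanner".
- **Dietary weight loss intervention:** "there will be a fasting blood draw at the midpoint of the study (week 12) to monitor blood chemistries (serum aminotransferases and lipids". FibroTest is not mentioned.

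The Fig. 1 legend includes FibroTest in the laboratory blood work without linking it to a visit. The figure itself is not available, so it cannot settle the matter.

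The Statistical analyses section names FibroTest among the primary measures, defines the endpoint as the 24-week change and assigns it to ANCOVA. It calls the primary analysis intent-to-treat but removes participants whose outcome is missing. For variables measured over time it adds that "a mixed model of repeated measures ANCOVA will be applied to examine the effect of treatment, time and their interaction", with body weight, satiety hormones and glucose as examples.

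**The concern.** FibroTest is a primary measure, so its visit schedule should read the same everywhere. Staff working from the primary outcome or dietary section would have no reason to order it at week 12; staff working from the laboratory section would.

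The missed value could not be recovered later. The primary outcome section lists the blood components of the score as gamma-glutamyl transpeptidase, bilirubin, α2-macroglobulin, haptoglobin and apolipoprotein A1. None of these is an aminotransferase or part of the lipid panel in the Fig. 1 legend (total, LDL, HDL, triglycerides).

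FibroScan and MRI are scheduled only at weeks 0 and 24. For someone who leaves between weeks 12 and 24, a week-12 FibroTest is therefore the only on-treatment value of any primary measure that could exist. At stake is whether that value is collected and, if so, whether the analysis uses it.

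**Working it through.** **1. Schedule of the primary measures, by section**

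| Section | Measure | Week 0 | Week 12 | Week 24 |
|---|---|---|---|---|
| Laboratory | FibroTest | yes | yes | yes |
| Primary outcome | FibroTest | yes | not listed | yes |
| Dietary intervention | FibroTest | – | not listed in the draw | – |
| Primary outcome | FibroScan, MRI | yes | not listed | yes |

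The laboratory and primary outcome rows give different FibroTest schedules, however the dietary section is read.

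**2. Would a week-12 value enter the primary test?** The primary test needs a week-0 and a week-24 value. A participant who leaves between weeks 12 and 24 has no week-24 value and is removed by the missing-outcome rule. The week-12 value therefore makes no difference to the test as written.

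**3. How many participants are affected?** Inputs from the Sample size calculation section: 60 recruited, 30 per group, dropout about 20%.

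- Expected dropouts: 60 × 0.20 = 12.
- Remaining per group: 30 × 0.80 = 24.
- Share of the 12 leaving after week 12: not given. At 0% the number is 0; at 100% it is 12, or 12/60 = 20% of those randomised.

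**4. Is power at stake?** Inputs from the same section: difference 0.08, SD 0.056, two-sided alpha 0.025, power 80%, stated n = 10 per group.

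- Reproducing the plan: n = 2 × (z₀.₉₈₇₅ + z₀.₈₀)² × (SD/difference)² = 2 × (2.241 + 0.842)² × (0.056/0.08)² = 2 × 9.505 × 0.49 = 9.3, rounded up to 10. This matches. The t-based version gives 10.7, or 11.
- Power at 24 per group: 0.08 / (0.056 × √(2/24)) = 4.95; 4.95 − 2.24 = 2.71; Φ(2.71) = 99.7%. The t-based figure is 99.5%.

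On the plan's own inputs, losing 6 per group leaves FibroTest power almost untouched. What remains is possible bias if those who leave late differ in response from those who stay. The document gives nothing from which to size that bias.

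**The case against.** The best defence is that neither shorter passage says only. The primary outcome section can be read as fixing when the endpoint is assessed, the dietary section as mentioning part of a panel, and the laboratory section as the full list. The full protocol or the missing figure may also settle it. This softens the conflict but does not remove it: the primary outcome sentence gives a measurement schedule for FibroTest, and it differs from the laboratory schedule.

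A reader might infer that two rival primary analyses apply to FibroTest, leaving the choice open once data are seen. The text does not support that. The ANCOVA rule names FibroTest and fixes the 24-week change. The mixed-model rule is general, follows the secondary outcomes and does not name FibroTest. Satiety hormones appear under both rules, so the rules are not mutually exclusive. What is unstated is the role of a week-12 value.

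A reader might also infer that the schedule conflict itself removes participants from the primary analysis. It does not; step 2 shows that the missing-outcome rule does so either way. Nor does the document tie any rule to a week-12 bilirubin or albumin result, so no consequence can be drawn from those.

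Finally, moving FibroTest to a repeated-measures model goes beyond correcting a schedule, and it treats FibroTest differently from FibroScan and MRI. That is a fair cost to state. Against it, the model is one the plan already uses, and the week-24 comparison stays the primary test.

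**Conclusion.** The point holds as an inconsistency in the schedule of a primary measure, together with an analysis rule that would waste the extra value. Between 0 and 12 of 60 participants could have a week-12 FibroTest as their only on-treatment value of a primary measure. That range rests on the plan's dropout of about 20%; any narrower range would need an assumption about when people leave.

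The consequence is limited to possible missing-data bias and to how far the intent-to-treat label is earned for FibroTest. Using the week-12 value would help only participants who reach week 12, and only so far as later missingness is explained by the values already observed. This is a worthwhile and inexpensive improvement, not a threat to the trial's power.

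**What to change.** 1. Amend the primary outcome and dietary intervention sections to agree with the laboratory section, so that FibroTest is explicitly drawn at weeks 0, 12 and 24. FibroScan and MRI stay at weeks 0 and 24.
2. In the Statistical analyses section, state that FibroTest is analysed with the plan's repeated-measures mixed model, with weeks 12 and 24 as outcomes and adjustment for baseline. The week-24 between-arm contrast is the primary test.
3. State that every participant with any post-baseline FibroTest is included, and limit the missing-outcome exclusion sentence accordingly.

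**Cost:** protocol wording. A week-12 fasting draw is already planned in both sections that mention one. If the short panel was intended, up to 60 additional FibroTest panels are needed. FibroTest would also be modelled differently from the other two primary measures, which the text should say openly.
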